## Abstract

**Background:**

Metabolic syndrome is a cluster of cardiovascular risk factors that greatly increase the risk of developing cardiovascular disease and type 2 diabetes. Regular exercise improves the risk profile, but most people do not successfully change their exercise habits to beneficially reduce risk. Tailored exercise prescribed by a family physician has shown promise as a means to increase fitness and reduce cardiometabolic risk, but optimal implementation practices remain unknown. Mobile health technologies have proved to be a beneficial tool to achieve blood pressure and blood glucose control in patients with diabetes. These technologies may address the limited access to health interventions in rural and remote regions. However, the potential as a tool to support exercise-based prevention activities is not well understood. This study was undertaken to investigate the effects of a tailored exercise prescription alone or supported by mobile health technologies to improve metabolic syndrome and related cardiometabolic risk factors in rural community-dwelling adults at risk for cardiovascular disease and type 2 diabetes.

**Methods/Design:**

Adults (*n* = 149) with at least two metabolic syndrome risk factors were recruited from rural communities and randomized to either: 1) an intervention group receiving an exercise prescription and devices for monitoring of risk factors with a smartphone data portal equipped with a mobile health application; or 2) an active control group receiving only an exercise prescription. All participants reported to the research centre at baseline, and at 12-, 24- and 52-week follow-up visits for measurement of anthropometrics and blood pressure and for a blood draw to test blood-borne markers of cardiometabolic health. Vascular and autonomic function were examined. Fitness was assessed and exercise prescribed according to the Step Test and Exercise Prescription protocol.

**Discussion:**

This study tested the effects of a prescriptive exercise intervention alone, versus one supported by mobile health technology on cardiometabolic risk factors. The intervention was designed to be translated into clinical or community-based programming. Results will contribute to the current literature by investigating the utility of mobile health technology support for exercise prescription interventions to improve cardiometabolic risk status and maintain improvements over time; particularly in rural communities.

**Trial registration:**

Clinical trials registration: NCT01944124

## Background

Cardiovascular disease is the leading cause of death worldwide accounting for 48% of mortality and 10% of global disease burden [1]. Cardiovascular complications are common in patients with type 2 diabetes mellitus, with heart disease responsible for 68% and stroke responsible for 16% of mortality in this patient population in the United States [2]. Metabolic syndrome is a defined set of risk factors including elevated blood pressure, dysglycemia, dyslipidemia and abdominal obesity, which increases the risk of developing cardiovascular diseases and type 2 diabetes mellitus [3,4]. Metabolic syndrome risk factors often present concurrently with other global cardiometabolic risk factors [4], ranging from standard clinical variables, such as low density lipoprotein and total cholesterol, high sensitivity C-reactive protein and body mass index to novel physiologic factors requiring specialized testing, such as vascular and autonomic function. While certain risk factors have been identified, it remains unclear which variables may be clinically important as early risk markers for cardiovascular complications. Early identification and management of these risk factors may be an important strategy for preventing cardiovascular diseases and type 2 diabetes mellitus.

Metabolic syndrome is highly treatable and lifestyle changes, including increased physical activity and regular exercise are recommended as first line treatment [4]. Longitudinal studies have shown that adoption of aerobic exercise training in healthy and sedentary middle-aged adults with metabolic syndrome improved the cardiometabolic risk profile and reduced the prevalence of metabolic syndrome [5-8]. Improved lifestyle behaviours in patients with metabolic syndrome are important to prevent the progression to chronic diseases, such as type 2 diabetes mellitus. The Diabetes Prevention Program tested an intensive lifestyle intervention with the goal of seven percent weight loss through a low-calorie, low-fat diet along with participation in a minimum of 150 minutes of moderate-to-vigorous physical activity per week [9]. This lifestyle intervention was more effective in preventing type 2 diabetes mellitus than pharmacological therapy with metformin or placebo plus standard lifestyle recommendations in overweight adults with impaired glucose tolerance [9]. At an average follow-up of 2.8 y, incident diabetes was 31% less in the metformin group and 58% less in the intensive lifestyle intervention group compared to the placebo group [9]. These studies highlight the importance of physical activity and exercise to manage risk and prevent progression to chronic disease.

Despite the known benefits of exercise, accelerometer data showed that 85% of Canadians [10] and 90% of Americans [11] do not meet physical activity guidelines. Exercise prescription in primary care may be an effective strategy to increase physical activity [12-14]. A systematic review concluded that exercise prescription interventions were effective at increasing physical activity, especially when they included a written prescription, considered behaviour change strategies and provided training and materials for physicians [14]. Despite known benefits, implementation in primary care remains low due to a gap in our understanding of how to best target and deliver individualized exercise prescriptions to patients at risk in the community.

In recent years, mobile technologies have been used as a medium for implementing health monitoring interventions. Mobile health has been used as a tool to support patient management of chronic diseases including type 2 diabetes mellitus [15] and hypertension [16-18], but little attention has been paid to leveraging mobile health technologies for risk management for disease prevention. To date, one pilot study examined the effects of a cardiovascular disease prevention intervention using an electronic health intervention with a mobile health component to manage metabolic syndrome risk factors [19]. The workplace electronic health program consisted of a four-week education module (60 minutes per session) plus access to telephone counseling, short message service messages and/or email messages for six months. Body fat, blood pressure and pedometer steps were regularly monitored. Following six months, waist circumference, systolic and diastolic blood pressure and triglycerides were reduced, with no changes in fasting plasma glucose or high density lipoprotein cholesterol [19]. This six-month eHealth intervention improved metabolic syndrome risk, but it was limited to a population of workers whose employers accepted the Healthy Workplace Program. Additionally, fasting plasma glucose was not monitored despite evidence from interventions in patients with type 2 diabetes mellitus supporting home-monitoring as an effective tool for improving fasting plasma glucose [15].

Access to healthcare is often reduced in rural compared to urban communities. For example, Huron County in rural southwestern Ontario has a 27.5% physician vacancy rate (number of positions available for general practitioners) compared to 0% vacancy rate in nearby urban centres [20]. Innovative technologies including mobile health monitoring have the potential to increase access to healthcare. Our group completed a pilot study testing the feasibility and utility of deploying a mobile health technology kit for self-management of metabolic syndrome risk factors and physical activity in a rural population [21,22]. Twenty-four participants aged 30-72 years monitored their blood pressure three times per week and blood glucose two times per day with Bluetooth™ enabled devices paired with a smartphone. Additionally, pedometer steps were manually inputted daily and body weight was inputted weekly [21,22]. A health monitoring system including an application on the smartphone and a secure online database was used to transmit and store data [21]. Alarms were triggered when measurements were outside of pre-determined limits. Following the eight-week intervention, waist circumference, diastolic blood pressure and total cholesterol were reduced, physical activity and fitness were increased [22], and autonomic function was improved [23]. Furthermore, participants reported that the technology assisted in adopting new practices to improve wellbeing and did not take too much time or interfere with activities of daily living [21]. This study, however, could not conclude whether the mobile health protocol had added benefit to the exercise prescription.

Therefore, the purpose of this trial was to investigate the effects of a mobile health supported exercise prescription, compared to exercise prescription alone on metabolic syndrome and other global cardiometabolic risk factors in individuals at risk for cardiovascular disease and type 2 diabetes. It was hypothesized that the primary outcome, systolic blood pressure, and secondary outcomes would be improved in both groups, but to a greater extent in the mobile health intervention group at 12 weeks and that these changes would be better maintained at 24 and 52 weeks in the intervention group with mobile health support compared with the active control group.

## Methods/Design

### Study design

This study was a randomized controlled trial with two intervention arms: 1) the intervention group, which received a tailored exercise prescription and a mobile health technology kit; and 2) the active control group, which received only a tailored exercise prescription. Adults aged 18-70 years were screened for inclusion. Participants (*n* = 149) presenting with at least two metabolic syndrome risk factors reported to the clinic (Gateway Rural Health Research Centre, Seaforth, Ontario, Canada) at baseline (V0) and for 12- (V1), 24- (V2) and 52-week (V3) follow-up visits.

#### *Recruitment and screening process*

This study was approved by the University of Western Ontario Research Ethics Board (Protocol #15828). Community-dwelling adults aged 18-70 years were recruited via newspaper or radio advertisement, flyers, referral from healthcare professional and word of mouth. Interested candidates contacted the study coordinator for telephone screening. Participants were eligible if they had two or more metabolic syndrome risk factors according to National Cholesterol Education Program Adult Treatment Panel III criteria: waist circumference ≥ 88 cm (women) or ≥ 102 cm (men); systolic blood pressure ≥ 135 mmHg and/or diastolic blood pressure ≥ 85 mmHg; fasting plasma glucose ≥ 6.1 mmol/L; triglycerides ≥ 1.7 mmol/L; and high density lipoprotein cholesterol ≤ 1.29 mmol/L (women) or ≤ 1.02 mmol/L (men) [24]. Exclusion criteria were: systolic blood pressure > 180 mmHg and/or diastolic blood pressure > 110 mmHg; type 1 diabetes; history of myocardial infarction, angioplasty, coronary artery bypass or cerebrovascular ischemia/stroke; symptomatic congestive heart failure; atrial flutter; unstable angina; unstable pulmonary disease; use of medications known to affect heart rate; second or third degree heart block; history of alcoholism, drug abuse or other emotional cognitive or psychiatric problems; pacemaker; unstable metabolic disease and orthopedic or rheumatologic problems that could impair the ability to exercise. Participants who passed the initial screening were booked for a V0 appointment. To facilitate scheduling of group mobile health technology training sessions, block randomization was used, such that all participants attending appointments during week one were allocated to the intervention group and all participants attending appointments during week two were allocated to the control group and so on.

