### Final eligibility screening at baseline visit

Participants who qualified for the study reported to the clinic following an eight hour fast. Participants were instructed to abstain from caffeinated or alcoholic beverages for 12 hours and intense physical activity for 24 hours prior to their study visits. Voluntary informed consent was obtained from all participants. Inclusion and exclusion criteria were verified by a medical history interview and by measuring metabolic syndrome risk factors.

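### The method named block randomization is described as alternation by calendar week, which made the arm foreseeable before consent and final eligibility checks

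*Protocol article*

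**What the plan says.** Under Study design, the article states: "This study was a randomized controlled trial with two intervention arms". The Methods/Design part of the abstract also says that participants were randomized.

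The mechanism appears only under Recruitment and screening process. The rule for the first week is "block randomization was used, such that all participants attending appointments during week one were allocated to the intervention group". The following week's attenders went to the other arm, and the article indicates only briefly that the pattern continued. The reason given is logistic: "To facilitate scheduling of group mobile health technology training sessions".

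The order of events is given in two adjoining sections:

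- First contact: "Interested candidates contacted the study coordinator for telephone screening".
- Booking: "Participants who passed the initial screening were booked for a V0 appointment".
- At the baseline visit (V0), under Final eligibility screening at baseline visit, consent is recorded first: "Voluntary informed consent was obtained from all participants". The eligibility check is described at the same visit: "Inclusion and exclusion criteria were verified by a medical history interview and by measuring metabolic syndrome risk factors".

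The 12-week analyses section plans an ANCOVA of change, adjusted for the baseline value of the outcome. Neither that section nor the 52-week analyses section names a term for enrolment week or calendar time. The limitations in the Discussion cover volunteer motivation and the study-supplied phones, but not allocation.

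**The concern.** Block randomization means random ordering within blocks. The procedure described has blocks (weeks) but no stated random ordering. If the weeks simply alternate, the next arm is always known.

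The order of events makes this matter. Once a candidate is booked into a week, the arm is settled, yet consent and the final eligibility decision are still to come. That leaves two openings for selection: the choice of week at booking, and the decision to consent or exclude at V0. Several exclusion criteria call for judgement, such as unstable metabolic disease or joint problems that could limit exercise.

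At stake is the comparability of the arms, on which the between-group comparison of systolic blood pressure depends. Adjusting for baseline systolic pressure handles imbalance in that one variable. It does not handle imbalance in motivation, comfort with technology or other factors related to later change.

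**Working it through.** **1. The sections side by side**

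| Step | What the article describes | State of the arm |
|---|---|---|
| Telephone screening | Candidate contacts the study coordinator | Not yet fixed |
| V0 booked | Follows a passed telephone screen | Fixed by the booked week |
| Consent | Described at V0 | Already fixed |
| Final eligibility | Verified at V0 | Already fixed |

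No step introduces a random sequence, a random order of weeks or concealment of the coming arm. The labels in the abstract and under Study design therefore claim a property that the described mechanism does not show.

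**2. The plan's own sample size**

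Inputs from Sample size calculation: difference 6 mmHg, SD 12 mmHg, two-sided 0.05, 80% power, 15% dropout.

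- n per group = 2 × (1.960 + 0.842)² × 12² / 6² = 62.79, rounded up to 63. This matches the article.
- 63 × 1.15 = 72.45, rounded up to 73. This also matches. Dividing instead, 63 / 0.85 = 74.1, would give 75. That small difference has no bearing on this point.

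The formula treats participants as independently allocated individuals.

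**3. Illustration: what a selection shift would do**

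The shift is an assumption, defined as what remains after baseline adjustment. The documents give no value for it.

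- SE of the difference = 12 × √(2/63) = 2.14 mmHg.
- False-positive rate with no true effect = 1 − Φ(1.96 − b/SE) + Φ(−1.96 − b/SE).

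| Assumed shift b (mmHg) | b/SE | Two-sided false-positive rate |
|---|---|---|
| 0 | 0 | 5% |
| 1 | 0.47 | 7.5% |
| 2 | 0.94 | 15.5% |
| 3 | 1.40 | 28.9% |

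This uses the unadjusted SE. If ANCOVA reduces the SE, the same residual shift weighs more.

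**4. Illustration: the week as unit of allocation**

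The number enrolled per week (m) and the within-week correlation (ICC) are also assumptions.

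- Design effect = 1 + (m − 1) × ICC.
- m = 3, ICC = 0.01: design effect 1.02. Required n = 62.79 × 1.02, rounded up to 65 per group. Power at 63 is 79%.
- m = 10, ICC = 0.05: design effect 1.45. Required n = 62.79 × 1.45, rounded up to 92 per group. Power at 63 is 64%.

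Over that range of m, the 149 participants would span about 149/10 = 15 to 149/3 = 50 enrolment weeks, each holding one arm only.

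**The case against.** The case for the plan has real substance.

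- **A random element is not ruled out.** The article does not say how the first week's arm or the order of weeks was set. A condensed article may leave that to a fuller protocol. This stands, so the fix must allow for documenting it. It does not remove the point, because the rule that is printed reads as alternation. A random start alone would also leave every later week predictable.
- **No steering is shown.** A reader might infer that staff knew the arm when booking and placed candidates accordingly. The article does not support that: it does not say who booked V0 or what they knew. It supports only the statement that the design did not prevent selection.
- **The size is unknown.** A reader might take a particular bias in mmHg as established. It is not; the figures in the working rest on assumed inputs.
- **The inference is not voided.** The article reports no results and draws no causal conclusion. What is weakened is the planned between-group comparison. Alternating weeks also keep the arms close in calendar time, so slow seasonal drift should be roughly balanced. Selection at entry is the larger worry.
- **Unblinding through the calendar.** Because 12, 24 and 52 are even, follow-up weeks would also separate the arms, and a reader might infer that this unblinded assessors. The article claims no blinding, the arms differ visibly in equipment, and clinic pressure was taken with an automated device. This adds little.
- **Group training.** A reader might say that individual training made weekly allocation unnecessary. Under Mobile health technology, individual sessions were a fallback for those who could not attend a group, so the logistic reason is not refuted.

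The mechanism is openly disclosed. That lets a careful reader see the problem, but it does not make the label accurate.

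**Conclusion.** The point holds in limited form. As written, allocation was by calendar week under a predictable rule with no stated random element, and the arm was fixed before consent and final eligibility checks. The terms randomized and block randomization are not supported by that description, and selection by arm was not prevented.

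Whether selection occurred, and its size and direction, cannot be determined from the article. For scale only, an assumed residual shift of 1 to 2 mmHg is 17% to 33% of the 6 mmHg target (1/6 to 2/6).

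The conclusion assumes that the closing words of the allocation rule mean continued alternation, and that booking, consent and eligibility followed the order in which they are described. The analysis plan is not shown, so the lack of further covariates in the article is not counted as an error in itself. Nothing in the article offsets the allocation problem.

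**What to change.** 1. **Describe the allocation accurately** in the abstract, Study design, and Recruitment and screening process. If a random element existed, such as a random order of weeks, document it, name the week as the unit of allocation and make the analysis reflect that. Otherwise call it alternating-week, quasi-randomised, unconcealed allocation. State who booked V0 and what they knew.
2. **Add allocation to the limitations** in the Discussion, and word the between-group inference accordingly.
3. **Report flow by arm**: numbers booked, attended, consented and excluded at V0, as far as records allow.
4. **Prespecify a sensitivity analysis** of the primary ANCOVA before outcomes are examined by arm. Add a calendar-time term, allow for clustering by week, and include prognostic baseline variables already collected: age, sex, medication, exercise self-efficacy and decisional balance. Each week contains one arm, so fixed indicators for every week would absorb the arm effect. Use a linear or smooth time term with a random week effect or cluster-robust standard errors. State whether the two scales were completed before participants learned their arm. These variables reduce measured imbalance only.

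With 149 recruited against 2 × 73 = 146 planned, changing the allocation itself is no longer in question. The cost is a less favourable design label, a few degrees of freedom and a little more analysis work. The analysis is still described in the future tense, so these changes remain possible.

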### Final eligibility screening at baseline visit

Participants who qualified for the study reported to the clinic following an eight hour fast. Participants were instructed to abstain from caffeinated or alcoholic beverages for 12 hours and intense physical activity for 24 hours prior to their study visits. Voluntary informed consent was obtained from all participants. Inclusion and exclusion criteria were verified by a medical history interview and by measuring metabolic syndrome risk factors.

### Laboratory procedures for baseline and follow-up visits

#### *Demographics and medical history*

During the baseline visit only, participant demographics recorded included: date of birth, sex, race and postal code. An interview was then conducted to determine medical history, which included documenting information regarding smoking status, alcohol consumption, history of heart/vascular disease, history of endocrine disease, gynecological history, lifestyle habits, past illnesses and surgeries, and current medications. While the full interview was conducted only at baseline, it was requested that participants contact the study coordinator should there be any change in any of these items and at each follow-up visit participants were asked if there was any change in medication or health status.

#### *Physical examination*

At each study visit, anthropometrics were measured. Body weight was measured with an automated scale and height was measured with a standard stadiometer in light clothing with shoes removed. Waist circumference was measured (to the nearest 0.5 cm) following a normal exhalation at the mid-point between the twelfth rib and superior boarder of the iliac crest [25]. Blood pressure was measured with an automated device (BPTru®, Coquitlam, Canada) in the supine position following a five-minute rest period. The average of the last two of three measures was used to determine resting blood pressure (to the nearest 1 mmHg). Participants continued to rest supine for an additional 30 mins after which research personnel certified in venipuncture drew blood from the anticubital vein. Blood was sent to a central laboratory (GammaDyna Care, London, Ontario) for analysis of fasting plasma glucose, lipid profile, glycated hemoglobin, insulin, high sensitivity C-reactive protien, catecholamines, and estrogen.

